### Anthropometry

Measures include body weight (kg), height (cm), and MUAC (mm). Weights of both mother and children are measured using the *SECA 874* electronic scale (to 0.1 kg accuracy). Height of children (standing and recumbent) and mothers are measured using the *SECA 250* scale (to 0.1 cm accuracy). Age is assessed by both presentation of birth certificate and recall by the mother/care taker using an events calendar. Standard numerical MUAC bracelets are used to record MUAC to the nearest mm. Measurements are taken twice and the average is recorded. All data enumerators are trained according to international recommendations. Standardised weight-for-height and height-for-age *Z* scores and percentiles are calculated as per the World Health Organisation (WHO) guidelines [19].

### Biochemical measures

Haemoglobin (Hb) g/dl is measured using the *HemoCue 201+* analyser (to 0.1 g/dl accuracy) and adjusted for pregnancy in women [20].

### Process evaluation

The process evaluation focuses on the implementation of the intervention which, together with the theory of change, contextual factors and data collected during the implementation, adds additional understanding of the observed study outcomes. Context data is collected through secondary sources and a community questionnaire and includes data on: supply-side availability and accessibility (e.g. health care, food, water - including cost and distance); local disease environment; social/political environment; cultural decision making and empowerment environment, other interventions that may influence the outcome (e.g. NGO/INGO, government programmes); the indirect impact on the traders and market development (including food price fluctuations).

All quantitative measures and time points are summarised in Table 2.

**Table 2 Tab2:** Outcome measures and intermediary factors and time points for all REFANI-P study groups

			Month						
		Baseline	1	2	3	4	5	6	12
Primary and secondary outcomes									
Child variables	Age (months)	x							
	Sex	x							
	Oedema	x	x	x	x	x	x	x	x
Anthropometry									
Child	Weight (Kg)	x	x	x	x	x	x	x	x
	Height/length (cm)	x	x	x	x	x	x	x	x
	MUAC (mm)	x	x	x	x	x	x	x	x
Mother	Weight (Kg)	x	x	x	x	x	x	x	x
	Height (cm)	x							
	MUAC (mm)	x	x	x	x	x	x	x	x
Biochemical (mother & child)	Haemoglobin (g/dl)	x						x	x
Child morbidity (presence, frequency, duration)	Diarrhoea	x	x	x	x	x	x	x	x
	Bloody diarrhoea	x	x	x	x	x	x	x	x
	Cough	x	x	x	x	x	x	x	x
	Difficulty breathing	x	x	x	x	x	x	x	x
	Fever	x	x	x	x	x	x	x	x
	Malaria	x	x	x	x	x	x	x	x
	Measles	x	x	x	x	x	x	x	x
	Health seeking	x	x	x	x	x	x	x	x
	Treatment (by whom)	x	x	x	x	x	x	x	x
	Long term health problems	x						x	x
Mother and child questionnaire									
Mother’s health	Age (years)	x							
	Perceived physical health	x	x	x	x	x	x	x	x
	Mental health [25]	x	x	x	x	x	x	x	x
	Pregnancy	x	x	x	x	x	x	x	x
Expenditures on child	Food, non-food, medical	x	x	x	x	x	x	x	x
	Source of money	x	x	x	x	x	x	x	x
Child care	Hours spent per week	x	x	x	x	x	x	x	x
Food security	Individual dietary diversity	x	x	x	x	x	x	x	x
Women’s empowerment	Autonomy	x						x	x
	Decision-making	x			x			x	
	Social capital	x						x	x
Household questionnaire									
Demographic data		x							
Household hygiene	Soap (access/availability)	x	x	x	x	x	x	x	x
	Hygiene score (from observation)	x	x	x	x	x	x	x	x
	Water storage	x	x	x	x	x	x	x	x
Wealth & employment	Satisfaction with life	x			x			x	x
	Productive assets (own, bought, sold)	x	x	x	x	x	x	x	x
	Other assets	x						x	x
	Number in employment	x	x	x	x	x	x	x	x
	Income (including sources)	x	x	x	x	x	x	x	x
	Employment status	x	x	x	x	x	x	x	x
	Hours worked per week	x	x	x	x	x	x	x	x
Expenditures	Food, non-food, medical	x	x	x	x	x	x	x	x
Food security	Household hunger	x	x	x	x	x	x	x	x
	Household dietary diversity	x	x	x	x	x	x	x	x
Coping	Causes of stress	x	x	x	x	x	x	x	x
	Coping mechanisms	x	x	x	x	x	x	x	x
	Migration	x	x	x	x	x	x	x	x
	Loans/debts (incl ability to repay)	x	x	x	x	x	x	x	x
	Schooling	x						x	x
Community questionnaire									
Demographic data		x							
Infrastructure & access		x							
Economic		x							
Health & education		x							
Social capital		x							
Process evaluation									
Implementation	Delivery to individuals				x			x	
	Response of individuals				x			x	

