**Methods/Design:**

The Research for Food Assistance on Nutrition Impact Pakistan study (REFANI-P) sets out to evaluate the impact of three cash-based interventions on nutritional outcomes in children aged less than five years from poor and very poor households in Dadu District. This four-arm parallel cluster randomised controlled trial is set among Action Against Hunger (ACF) programme villages in Dadu District, Sindh Province. Mothers are the target recipients of either seasonal unconditional cash transfers or fresh food vouchers. A comparison group receives ‘standard care’ provided by the ACF programme to which all groups have the same access. The primary outcomes are prevalence of wasting and mean weight-for-height Z-score (WHZ) in children. Impact will be assessed at 6 months and at 1 year from baseline. Using a theory-based approach we will determine ‘how’ the different interventions work by looking at the processes involved and the impact pathways following the theory of change developed for this context. Quantitative and qualitative data are collected on morbidity, health seeking, hygiene and nutrition behaviours, dietary diversity, haemoglobin concentration, women’s empowerment, household food security and expenditures and social capital. The direct and indirect costs of each intervention borne by the implementing organisation and their partners as well as by beneficiaries and their communities are also assessed.

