### Planned statistical analysis

The study will use both quantitative and qualitative data analytical methods and a cost-effectiveness analysis will be done. The key steps for the quantitative data analysis of outcome measurements will be: 1) cluster level analyses using summary measures between the different time points and 2) individual level analyses adjusted for clustering (longitudinal generalised mixed models). Significance will be assessed at *p* < 0.05 level.

Baseline descriptive analyses will be carried out on all independent variables at cluster and individual levels to assess baseline differences between groups. The data will be examined for outliers, normality and missing data. To test the overall effect of the interventions (on an intention-to-treat basis), changes in outcome variables between the different groups over follow-up measurements (6 months and at 1 year) will be compared. The interventions, measurement time and intervention-time interaction will be included as fixed effects in the models. Children, mothers and villages will be included as random effects in the intercept and in the slope of the different repeated measurements. Potential confounders (e.g. sex, age and baseline nutrition status) will be used if there are differences at baseline. Best fit of the data will be assessed using maximum likelihood ratio tests.

We will examine the data to determine the extent and type of differential attrition, and depending on our findings, we may apply an appropriate adjustment to estimates of intervention effect and/or discuss the possible consequences they may have on the reliability of the estimates. Since there will be more than one child per household in many cases, a secondary analysis using one child per household (selected at random) will be carried out to confirm if results are being driven by a smaller number of larger households. A mediation analysis (using seeming unrelated regression methods [22–24]) will be carried out to measure the extent to which increased mediating variables may mediate the relationship between the different interventions and comparison group and wasting. All quantitative analyses will be carried out in Stata 13.1. Z-scores will be generated using the World Health Organisation (WHO) macro for Stata.

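### Table 2 schedules women's decision-making at baseline, month 3 and month 6 but not month 12, so no effect on it at 1 year, or after transfers stop, can be estimated quantitatively

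*Protocol article*

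**What the plan says.** The Process evaluation section of the protocol article introduces its schedule with "All quantitative measures and time points are summarised in Table 2", so the table is offered as complete. Its columns are "Baseline 1 2 3 4 5 6 12". Under women's empowerment, the decision-making row reads "Decision-making x x x", with marks under baseline, month 3 and month 6. Social capital, in the same group, reads "Social capital x x x", but its marks fall under baseline, month 6 and month 12. Autonomy has the same pattern as social capital.

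The Abstract states "Impact will be assessed at 6 months and at 1 year from baseline". The Study design section places the transfers in six consecutive months and the final data collection six months after they end. The Outcome measures section gives a general schedule of months 0 to 6 and 12 for the household questionnaire and the mother and child questionnaire. The Planned statistical analysis section adds that a mediation analysis "will be carried out to measure the extent to which increased mediating variables may mediate the relationship between the different interventions" and the comparison group, and wasting. It names no mediators and fixes no time points for them.

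**The concern.** The transfers go to mothers, and the trial sets out to explain how they work as well as whether they do. Control over household decisions is one plausible route, and women's empowerment is one of the data domains the Abstract names. The closed cohort is followed for six months after the last transfer, which allows a check on whether changes last once payments stop. For decision-making that check is not scheduled. Both of its follow-up measurements fall while transfers are being paid or just after the last one. If a gain at month 6 faded by month 12, or held, the quantitative data could not show it. The two sibling empowerment items would show it for their own constructs.

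**Working it through.** No sample size, power or error-rate figure is involved, and the plan gives no figure to reproduce. The check is a cell-by-cell reading of Table 2 against its eight-column header.

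| Row | Months marked | Month 12? |
|---|---|---|
| Decision-making | 0, 3, 6 | no |
| Autonomy | 0, 6, 12 | yes |
| Social capital (mother and child questionnaire) | 0, 6, 12 | yes |
| Satisfaction with life | 0, 3, 6, 12 | yes |
| Child weight | 0, 1, 2, 3, 4, 5, 6, 12 | yes |
| Delivery to, and response of, individuals (implementation) | 3, 6 | no |

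1. **Rounds covered.** Decision-making has 3 of 8 rounds. Baseline aside, that is 2 of 7 follow-up rounds. Only one round, month 12, lies after the transfer period, and coverage there is 0 of 1.

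2. **Is the pattern shared?** The mother and child questionnaire block has 11 rows. Mother's age is baseline only, which leaves 11 − 1 = 10 rows with follow-up. Nine of these reach month 12, and decision-making is the exception. In the rest of the table, every outcome or intermediary row with any follow-up also reaches month 12. The only other rows that stop at month 6 are the two implementation rows, and these describe delivery, which itself ends then.

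3. **Is the month-3 visit the explanation?** Satisfaction with life is the closest comparator: "Satisfaction with life x x x x". It has the same baseline, month-3 and month-6 marks and then continues to month 12. A lighter schedule during the intervention therefore does not imply stopping at month 6.

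4. **What can be estimated.** Arm differences in decision-making can be estimated at months 3 and 6. An arm-by-time term at month 12 cannot, because there are no observations. For autonomy and social capital it can.

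5. **What is untouched.** Child weight reads "Weight (Kg) x x x x x x x x", and child height or length and oedema follow the same schedule, so wasting and WHZ are available at both impact time points. Decision-making is not among the primary or secondary outcomes under Outcome measures. For mediation, a month-3 value precedes wasting at month 6, and month-3 and month-6 values both precede wasting at month 12.

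**The case against.** The strongest reply is that nothing planned depends on the missing value. A reader might infer from the blank cell that the 1-year impact analysis and the pathway analysis cannot include decision-making. The document does not support that. The comparison at 6 months and 1 year concerns outcome variables, and decision-making is not a listed outcome. A mediator should come before its outcome, so a month-6 value is properly ordered for 12-month wasting, whereas a month-12 value would be concurrent with it. A reader might also infer that a three-part empowerment comparison at 1 year has lost a part, but the article plans no such comparison or composite. Nor can the weight of decision-making in the theory of change be judged, since no mediators are named and the figure is not shown. All of this stands.

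The schedule may also be deliberate, since months 3 and 6 are the rounds used for the implementation rows. That is possible, but the article does not say so, and the other two empowerment items are scheduled differently.

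The qualitative tracer study does look at households after transfers end. It can describe what happened to decision-making, but interviews and case narratives do not give a randomised comparison across four arms.

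The general schedule under Outcome measures, which includes month 12 for the mother and child questionnaire, conflicts with the blank cell only weakly, because several rows skip rounds within that schedule.

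**Conclusion.** The point holds as a minor gap in the measurement schedule. Decision-making is the only followed-up outcome or intermediary factor without a month-12 value, and no reason is stated. As a result, neither the effect of each arm on it at 1 year nor its persistence after transfers stop can be estimated quantitatively. The size is one variable at one of the two impact time points, in all four arms. The primary and secondary comparisons and the sample size are not affected, and mediation models for wasting at either time point remain possible with the earlier values.

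The conclusion assumes that Table 2 is the operative schedule and that the blank cell reflects it. If the blank is only a dropped mark, the defect is in the table and not in the data. The document does not settle which.

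**What to change.** Add the decision-making items used at baseline and month 6, unchanged, to the month-12 mother questionnaire, and mark month 12 in that row of Table 2. If the items are already in the endline questionnaire, correct the table only. If the omission was intended, state the reason and say that persistence of decision-making will not be assessed quantitatively.

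The month-12 interview already takes place and already covers autonomy and social capital, so no extra visit or staff is needed. The cost is a few more questions and a slightly longer endline interview. The article lists the trial as ongoing. If endline collection is already complete without these items, the gap should be reported as a limitation.

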### Qualitative study

Empirical qualitative data are collected during the study period, using key informant interviews, focus group discussions, in-depth interviews and individual case narratives (ICN) of study participants. Information is gathered from purposefully selected key informants such as recipients across intervention groups (as well as non-recipients within the villages), research mobilisers, REFANI and ACF staff, those working in different capacities in health, education, public administration, and people working in other organisations that are present for providing assistance to the local population.

A longitudinal qualitative research tracer study (QRTS) is designed to incorporate time and change into the research process. This is carried out though the in-depth interviews and ICNs. The QRTS documents the dynamics of household behaviours and captures critical moments and processes involved in the changes in recipients’ lives as a result of the intervention, and other external events that they are exposed to. The QRTS is particularly helpful in capturing ‘transitions’ experienced by individuals and families following the intervention, and in understanding factors that support or hinder household development once they stop receiving the intervention.

### Economic evaluation

Several data sources are used to assess and analyse the total resource use of each intervention modality, namely ACF accounting data, focus group discussions and interviews with ACF and partner organisation staff, community key informant interviews, focus group discussions with beneficiaries, and survey data. Institutional costs are primarily assessed using accounting data, along with staff interviews. Additional financial costs which are not included in the ACF programme accountancy such as any costs from other institutional partners or other important costs which have been allocated to other programme budgets, etc., are identified through key informant interviews and review of programme documentation.

Societal costs are assessed using qualitative and quantitative methods. Focus group discussions with beneficiaries are conducted to better understand the costs borne by beneficiary households and their communities to be able to receive the transfers. In order to triangulate the data collected on direct and indirect programme costs to beneficiaries, questions relevant to the CEA have been included in the household questionnaire conducted at the 6 month mark of the study.

Staff time allocation is assessed to enable an activity-based costing (ABC) methodology, and to allocate and estimate costs per major program activity.

### Sample size

To determine the minimum detectable difference in prevalence of wasting for this sample size the following information was used: 1) estimated prevalence of wasting at baseline (16 %); 2) an estimate of the intra-class correlation coefficient (ICC) from a previous survey (0.02); 3) an estimate of the average cluster size (50); 4) for unequal cluster sizes an estimate of the coefficient of variation of cluster sizes (0.65); 5) significance level at 5 % and power of at least 80 %; 6) a likely dropout rate of 10 %; and 7) the estimated number of eligible children per household (2.2).

The sample size is 632 households per intervention group. This sample size is sufficient to measure a detectable difference of 7 % between the intervention groups and the comparison group post intervention. The sample is powered to detect a 0.19 WHZ difference between the intervention and comparison groups (based on a baseline mean of −1.22 (1.10), from previous data).

Sample size calculations were carried out in Stata (SE version 13.1; StataCorp, Special Edition, College Station, Texas 77845 USA) using the [*clustersampsi*] command.

### Randomisation

The unit of randomisation is villages stratified by village size (blocks of small, medium and large) to achieve similar numbers of children in each intervention group of the study and ensure an equal distribution of variables at baseline. Due to the likelihood of tensions between villages being created through a public randomisation process, randomisation is done separately by the principal investigator (PI) putting village names into a bowl and drawing out one at a time to add to an ‘intervention’ bowl.

### Data collection and management

Three Field Officers are supervising 24 teams, each made up of 1 female and 1 male enumerator. Research Mobilisers are available to help the teams in identifying households and sensitisation about the study.

Quantitative data is collected using ODK software which is a freely available application to design surveys for data collection through smart devices and run on android based platforms. The data are exported into password protected MS Excel on a daily basis and sent to the principal investigator. During the study, children identified with WHZ < −2 (using MOYO charts) [21], MUAC <125 mm and/or oedema are referred to the ACF outpatient treatment programme, whilst remaining in the REFANI-P study. Children with a haemoglobin level < 11.0 g/dl, non-pregnant women <12 g/dl and pregnant women <13 g/dl) are referred for Government of Pakistan nearest health facility for standard treatment.

Qualitative data are being collected by a team of three led by a local lead researcher. Interviews are being recorded then transcribed and translated into English within a week of data collection. The focus group discussions relevant to the cost-effective analysis (CEA) are recorded, transcribed and translated into English. The interviews are also recorded and transcribed and translated if deemed necessary during the course of data collection. Relevant data from the impact study are extracted from the quantitative data set in ODK as described above.

### Planned statistical analysis

The study will use both quantitative and qualitative data analytical methods and a cost-effectiveness analysis will be done. The key steps for the quantitative data analysis of outcome measurements will be: 1) cluster level analyses using summary measures between the different time points and 2) individual level analyses adjusted for clustering (longitudinal generalised mixed models). Significance will be assessed at *p* < 0.05 level.

Baseline descriptive analyses will be carried out on all independent variables at cluster and individual levels to assess baseline differences between groups. The data will be examined for outliers, normality and missing data. To test the overall effect of the interventions (on an intention-to-treat basis), changes in outcome variables between the different groups over follow-up measurements (6 months and at 1 year) will be compared. The interventions, measurement time and intervention-time interaction will be included as fixed effects in the models. Children, mothers and villages will be included as random effects in the intercept and in the slope of the different repeated measurements. Potential confounders (e.g. sex, age and baseline nutrition status) will be used if there are differences at baseline. Best fit of the data will be assessed using maximum likelihood ratio tests.

We will examine the data to determine the extent and type of differential attrition, and depending on our findings, we may apply an appropriate adjustment to estimates of intervention effect and/or discuss the possible consequences they may have on the reliability of the estimates. Since there will be more than one child per household in many cases, a secondary analysis using one child per household (selected at random) will be carried out to confirm if results are being driven by a smaller number of larger households. A mediation analysis (using seeming unrelated regression methods [22–24]) will be carried out to measure the extent to which increased mediating variables may mediate the relationship between the different interventions and comparison group and wasting. All quantitative analyses will be carried out in Stata 13.1. Z-scores will be generated using the World Health Organisation (WHO) macro for Stata.

Recorded speech or transcribed text, obtained from qualitative research tools, will be analysed using NVivo 10 for windows software (© QSR International Pty Ltd 2014). Qualitative data will be checked and cleaned prior to analysis. Data obtained from different sample groups, as defined by a range of different criteria (e.g. men and women, interventions and controls, etc.) will be contrasted to explore how the different interventions have been perceived and understood and their effect on different participants. The multidimensional analysis is expected to be cross-sectional at each time point to allow analysis between individuals at the same time period, as well as longitudinally capturing each individual and household’s narrative. Analysis will be carried out on 3 levels: thematic, semiotic and a narrative analysis.

The data analysis for the cost-effectiveness study will be based on the institutional, beneficiary and community level quantitative and qualitative data sets, and will be done using Microsoft Excel and TreeAge softwares (TreeAge Pro Healthcare. Williamstown: TreeAge; 2012). Qualitative data will be analysed for themes and contextualising factors. Cost-effectiveness ratios will be calculated as incremental cost-effectiveness ratios (ICER), representing the additional cost per improved outcome achieved in one intervention compared to another intervention or to standard care. Other cost metrics, such as cost per beneficiary, cost-transfer ratio, etc. will also be calculated. A sensitivity analysis will be performed to gain insight into cost drivers, and to determine how sensitive the cost-effectiveness results are to a significant but plausible variation in each of the most important cost parameters.

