### Outcome measures

Measurements are collected on all study households (household questionnaire) and participants (mother and child questionnaire) at month 0, 1, 2, 3, 4, 5, 6 and 12. Measurements are collected during the week following the receipt of each transfer. The primary outcomes are prevalence of wasting (as measured by WHZ < −2 or the presence of bilateral pitting oedema) and mean WHZ score in children.

Secondary outcomes are:in children - cumulative incidence of wasting, prevalence of SAM (<−3 WHZ), low mid-upper arm circumference (MUAC) (<125 mm & < 115 mm), stunting (<−2 height-for-age z-score) and morbidity (mainly diarrhoea, difficulty breathing/cough, malaria)in mothers and children - mean haemoglobin concentration (Hb g/dL) and prevalence of anaemia (children: Hb <11.0 g/dL; severe anaemia as Hb < 7.0 g/dL; non-pregnant women Hb <12.0 g/dL; pregnant women Hb <13.0 g/dL)in mothers - prevalence of low body mass index (<16, <17, <18.5 kg/m^2^), low height (<145 cm) and low MUAC (<230 mm & <210 mm).

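### Adding baseline covariates as main effects would barely change the change contrast being tested, and a prespecified baseline-adjusted model would be more precise

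*Protocol article*

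**What the plan says.** The point concerns the second analysis step in the protocol article's Planned statistical analysis section: "individual level analyses adjusted for clustering (longitudinal generalised mixed models".

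- Comparison: "changes in outcome variables between the different groups over follow-up measurements (6 months and at 1 year) will be compared".
- Fixed effects: "The interventions, measurement time and intervention-time interaction will be included as fixed effects in the models".
- Random effects: "Children, mothers and villages will be included as random effects in the intercept and in the slope of the different repeated measurements".
- Covariates: "Potential confounders (e.g. sex, age and baseline nutrition status) will be used if there are differences at baseline". No covariate-by-time term is mentioned.

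Under Outcome measures, "The primary outcomes are prevalence of wasting (as measured by WHZ < −2 or the presence of bilateral pitting oedema) and mean WHZ score in" the study children, with measurements "at month 0, 1, 2, 3, 4, 5, 6 and 12". Table 2 records child age and sex at baseline only.

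The section does not say whether month 0 is a row of the outcome, whether the arms have separate or common month-0 means, or which coefficient is the effect.

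**The concern.** Comparing changes through an arm-by-time interaction most naturally means that month 0 is an outcome row and that the effect is each arm's change from month 0 minus the comparison arm's change. If raw follow-up rounds alone were modelled, the interaction would compare changes between follow-up rounds, which is not the intervention effect.

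On that reading two things follow. First, the covariates named are constant within a child. As main effects they shift all of a child's rounds by the same amount, so they have almost no leverage on a difference in change. Baseline WHZ would also be predicting itself at month 0. This is separate from the usual objection to adjusting only on observed imbalance, because always entering the covariates in this way would not help either. Second, a free baseline mean per arm ignores that randomisation makes these means equal in expectation, and this costs precision.

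At stake are an adjustment step that does little of what it is meant to do, and avoidable variance in both primary outcomes.

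**Working it through.** **1. The plan's own figure.** The Sample size section gives ICC 0.02, mean cluster size 50, CV 0.65, 632 households per group, 2.2 children per household, 10% dropout, WHZ SD 1.10, and "significance level at 5 % and power of at least 80" per cent (taken as two-sided).

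- Design effect = 1 + [(1 + 0.65²) × 50 − 1] × 0.02 = 2.4025.
- Children per arm after dropout = 632 × 2.2 × 0.9 = 1251; effective n = 1251 / 2.4025 = 521.
- Detectable WHZ difference = (1.960 + 0.842) × 1.10 × √(2/521) = 0.191.

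This agrees with the stated 0.19. It is a post-intervention comparison that makes no use of baseline.

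**2. What main-effect covariates do to the interaction.** Data with villages and children were simulated at month 0 and two follow-up rounds. The arm-by-time model was fitted with and without a time-constant covariate, and then with baseline WHZ added. There were two data sets per linear setting and three for the logistic model, which had a child random intercept.

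| Setting | Largest shift, covariate only | Largest shift, baseline WHZ added |
|---|---|---|
| Linear, complete, random intercepts only (equal or unequal villages) | 0 | 0 |
| Linear, complete, random slopes, equal villages | 0 | 0 |
| Linear, complete, random slopes, unequal villages | 0.004 WHZ | 0.008 WHZ |
| As above, about 10% dropout | 0.004 WHZ | 0.007 WHZ |
| Logistic mixed model for wasting | 0.0005 log-odds | 0.012 log-odds |

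The shift is exactly zero only in the first two rows. Elsewhere it is small beside the 0.19 WHZ target.

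**3. Precision.** Let r be the correlation between baseline and follow-up arm means, with equal variances at the two times. Each of months 6 and 12 is treated as a two-time-point contrast. Relative to a follow-up-only comparison without baseline:

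- change contrast: variance 2(1 − r);
- baseline-adjusted or common-baseline contrast: variance 1 − r²;
- ratio: 2(1 − r)/(1 − r²) = 2/(1 + r).

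The detectable difference is 0.191 times the square root of each factor. The article gives no r, so a range is shown.

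| r (assumed) | Variance ratio | Detectable WHZ, change | Detectable WHZ, baseline-adjusted |
|---|---|---|---|
| 0.3 | 1.54 | 0.226 | 0.182 |
| 0.5 | 1.33 | 0.191 | 0.165 |
| 0.7 | 1.18 | 0.148 | 0.136 |
| 0.8 | 1.11 | 0.121 | 0.115 |
| 0.9 | 1.05 | 0.085 | 0.083 |

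With separate correlations for villages (0.5 to 0.8) and children (0.5 to 0.85), simulation gave ratios of 1.10 to 1.31.

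**4. Over-subtraction.** In those simulations the change contrast correlated −0.30 to −0.49 with the chance baseline difference; the baseline-adjusted contrast correlated about 0. The SE of a baseline WHZ difference between two arms is 1.10 × √(2 × 2.4025/1390) = 0.065, where 1390 = 632 × 2.2. A gap above 0.10 therefore has about a 12% chance for a given pair. For r of 0.6 to 0.8, a share 1 − r of the gap, that is 0.02 to 0.04 of each 0.10, is subtracted in excess.

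This is not a loss on top of step 3. Since 2(1 − r) = (1 − r²) + (1 − r)², the second term is exactly the variance due to over-subtraction.

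**The case against.** The strongest objection is that month 0 as an outcome row is inferred. The article speaks of follow-up measurements at 6 months and 1 year and lists baseline status as a possible covariate. That could describe a follow-up-only model, in which adjusting for baseline is ANCOVA and does move the estimate. An article may also leave row structure and covariate-by-time terms to an analysis plan. This stands as a limit on the point, which is conditional on the natural reading. Under the other reading the adjustment would work, but would still depend on observed imbalance.

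A reader might go further than the documents allow in five ways.

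- *The covariates leave the effect exactly unchanged.* Not under this plan, which has random slopes, unequal villages, expected dropout and a binary primary outcome. The estimate moves, though by little.
- *Baseline imbalance goes uncorrected.* Only the covariate step is nearly inert. The change contrast itself subtracts the whole baseline gap, which is too much rather than too little.
- *The effect is biased.* Under randomisation the change contrast is unbiased, and its standard error already carries the chance imbalance. No type I error problem follows.
- *The trial is underpowered as a result.* The sample size rests on a post-intervention comparison, and 0.19 reproduces. At r of 0.5 the change contrast matches it, and at higher r it does better.
- *A common baseline mean is free of risk.* It assumes that household enrolment was not influenced by village allocation. The Recruitment and Randomisation sections do not say whether the draw came before consent.

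**Conclusion.** The concern holds as a point about efficiency and about an adjustment step with little effect. If month 0 is in the outcome, covariates entered as main effects change the tested interaction by no more than about 0.008 WHZ or 0.012 log-odds in the settings tried, so the conditional step adds almost nothing. The planned contrast has about 11% to 33% more variance than a baseline-adjusted one for r of 0.8 to 0.5. For WHZ that is a detectable difference of 0.148 rather than 0.136 at r = 0.7, with a larger gap at lower r and a negligible one near 0.9.

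These sizes rest on assumed correlations, equal variances over time and the natural reading of the model. Validity under randomisation and the published sample size are not in question.

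**What to change.** Prespecify one model for the primary outcomes, to be used whatever imbalance is seen:

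- follow-up rounds only as outcomes, with the baseline value and its interaction with round as covariates; or
- a constrained longitudinal model with month 0 as an outcome row, one common month-0 mean for all four arms, and arm effects at follow-up rounds only.

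Any further covariate, such as age or sex, should also be interacted with round. State which coefficients are the 6-month and 1-year effects.

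The cost is a change of parameterisation, using a baseline value already collected for every child. The small downside lies in the second option's assumption about enrolment. If village allocation was known before households consented, use the first option, which does not force the arm baselines to be equal.
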